## Abstract

**Background:**

Irritable bowel syndrome (IBS) is a chronic, recurring condition, prevalent in the general population. Current medication treatments usually leave patients undertreated. Nowadays, Chinese medicine (CM) is being considered as a promising treatment approach for IBS. However, due to methodological limitations, there is no strong evidence to support CM. Although IBS relapses are common, the relapse assessment has always been neglected in CM study designs. Meanwhile, in clinical practice and studies, it has been found that certain CM formulas can only benefit certain kinds of patients. Discovering what population and illness characteristics likely respond to outcomes may help improve the effectiveness of CM. The aims of this study are to evaluate the efficacy and safety of *Tiao-Chang Ke-Min* (TCKM) granules for IBS, especially in reducing IBS symptoms’ relapse, by a high-quality randomized controlled trial and then to optimize the indication of the TCKM granules.

**Methods/design:**

This is a parallel-group, randomized, double-blind, placebo-controlled trial embedded with outcome predictive factors. Eligible patients with diarrhea-predominant IBS will be randomized into either a TCKM granule group or a placebo group. Patients from both groups will receive health education. The treatment duration is 4 weeks and the follow-up is 12 weeks. The primary outcome is global improvement measured with adequate relief (AR). The second outcome measures include time until relief, time until first relapse, total relapse times, long-term effectiveness, individual symptoms, IBS-Symptom Severity Score (IBS-SSS), IBS-Quality of Life Questionnaire (IBS-QOL), and Hospital Anxiety and Depression Scale (HADS). Predictive factors associated with patient and illness characteristics have been widely collected. These factors will be embedded in this trial for further identification.

**Discussion:**

This trial may provide high-quality evidence on the efficacy and safety of TCKM granules for IBS and a more accurate indication. Importantly, this trial will provide a new research method for improving the therapeutic effects of CM for clinicians and researchers. To address IBS relapse assessment, a series of special definitions of relapse incidents has been made for this trial.

**Trial registration:**

Chinese Clinical Trial Registry, ID: ChiCTR-IOR-17010600. Registered on 9 February 2017.

**Electronic supplementary material:**

The online version of this article (10.1186/s13063-018-2754-9) contains supplementary material, which is available to authorized users.

## Background

Irritable bowel syndrome (IBS) is a chronic, recurrent, and functional gastrointestinal disorder. It is very common, affecting between 5 and 20% of the general population worldwide [1, 2] and 4.6–6% of the population in China [3, 4]. IBS is a heterogeneous disorder with a complex pathogenesis, making treatment challenging [5]. There has been no consensus on the specific and effective strategies for the treatment of IBS. Current medication treatments are mainly based on relieving abdominal symptoms [6]. Therefore, many IBS patients remain undertreated or dissatisfied with their quality of life [7]. In addition, the long-term effectiveness of treatments is not good enough, as a systematic review concluded, through long-term follow-up, that only about 30% of IBS patients’ symptoms improved or disappeared [8]. Recently, more and more IBS patients have sought to treat their symptoms with complementary and alternative medicine [9].

At present, Chinese medicine (CM) is considered a promising approach in the treatment of IBS. CM is, by nature, multi-targeted. It can manage IBS through simultaneously acting on diversified pathways and mechanisms [10]. Clinical trials of CM for IBS have shown that CM could provide effective improvement in single symptoms, global assessments, and quality of life with few adverse events reported [11, 12]. However, according to current reviews, due to a lack of rigorous larger clinical trials, there is no strong evidence supporting CM in the treatment of IBS [7, 13, 14]. Furthermore, although IBS relapses are common, relapse incident assessment has always been neglected in CM study design [15].

One thing related to the effectiveness of CM should be given particular attention. CM treatment is a system of individualized medicine. The development of a CM formula is specific for a group of patients who share the common characterizes based on CM theory. In clinical practice and studies, it has been found that CM formulas may lead to a benefit improvement in some of the patients, but not in all. Finding out what patient and illness characteristics likely respond to CM treatment may help to identify a more suitable patient population, and improve the effectiveness of CM [16]. Similar studies have been conducted in psychological therapy for IBS [17–19]. These studies identified factors predicting a good or poor outcome, which was expected to provide helpful suggestions for clinicians. However, until now, there have been no studies looking specifically at predictive factors of treatment outcome in CM trials for IBS.

*Tiao-Chang Ke-Min* (TCKM) granules were developed by [name], a famous practitioner of CM in China. They can play a crucial role in addressing the core pathogenesis and causes of IBS, according to CM theory. TCKM granules have an effect on reducing IBS symptom relapse, and its effectiveness and safety have been confirmed through long-term clinical practice. To date, however, there have been no high-quality studies conducted to test its effectiveness.

We plan to perform a randomized controlled trial embedded with comprehensive outcome predictive factors, for the purpose of establishing high-level evidence and setting an example for optimizing the indication of IBS treated with CM.

### Trial purpose

The specific objectives of this trial are as follows:To assess the efficacy and safety of TCKM granules for IBS, especially in reducing IBS symptom relapseTo investigate what patient and illness characteristics may predict a successful outcome from the treatment of TCKM granules, and optimize the indication.

## Methods/design

### Design

This is a parallel-group, double-blind, randomized, placebo-controlled trial. The trial will include three periods: a 1-week run-in period, a 4-week treatment period, and a 12-week follow-up period. During the run-in period, patients who fulfill the screening criteria will record a symptom diary every day, and stop taking any drugs that the trial forbids. Those, who record all items in the symptom diary for at least 5 days during the run-in period and remain eligible will be randomized at a ratio of 1:1 into either the TCKM granule group or the placebo group. Visits will be scheduled at weeks 0–16 (or at discontinuation) to assess treatment efficacy, recurrence of IBS symptoms, and occurrence of adverse events. Additionally, comprehensive predictive factors associated with patient and illness characteristics have been collected through a series of qualitative methods. These factors will be embedded in this trial for further identification. (See Figs. 1 and 2). The protocol design is based on the Standard Protocol Items: Recommendations for Interventional Trials (SPIRIT) Checklist (Additional file 1).

**Fig. 1 Fig1:**
[figure not shown]
Flowchart of study. *TCKM Tiao-Chang Ke-Min*

**Fig. 2 Fig2:**
[figure not shown]
Study schematic diagram. *TCKM Tiao-Chang Ke-Min*, *IBS* irritable bowel syndrome, *AR* adequate relief, *IBS-SSS* IBS Symptom Severity Score, *IBS-QOL* IBS-Quality of Life Questionnaire, *HADS* Hospital Anxiety and Depression Scale, *AE* adverse event, *ECG* electrocardiogram

### Participants

#### Setting and recruitment

The trial will be conducted at three branches of the Guangdong Provincial Hospital of Chinese Medicine (GPHCM), Guangzhou, China: (1) Dade Road Hospital, (2) Ersha Island Hospital, and (3) Guangzhou University City Hospital. The recruitment of participants for this trial will be mainly via physician referrals from the gastroenterology clinics. Advertisements and colored fliers will also be placed inside the hospitals. Those who are willing to participant in this trial will need to contact the research assistants by telephone.

#### Diagnostic criteria

Diagnosis of IBS must meet the ROME IV criteria [20]. Among IBS subtypes, participants will be included in the type of diarrhea-predominant IBS. However, CM patterns of patients will not be restricted.

#### Inclusion criteria

Diagnosis with diarrhea-predominant IBS18 to 75 years of age, male or femaleSigned informed consentA reported Irritable Bowel Syndromes Symptom Severity Score (IBS-SSS) of > 75

#### Exclusion criteria

Patients with alarm symptoms such as severe weight loss in the past few months and hematocheziaPatients with history or current evidence of inflammatory bowel diseasePatients with history or current evidence of celiac disease, concurrent enteric infection, hyperthyroidism or other diseases causing diarrhea and abdominal painPatients who report a score of > 50 on the Self-rating Anxiety Scale (SAS) or a score of > 53 on the Self-rating Depression Scale (SDS), or patients with other psychiatric disordersPatients with a history of gastrointestinal surgery causing ailments similar to IBSPatients who are unable or unwilling to stop taking medication affecting the assessment of experimental drug efficacy and safetyPatients who are pregnant, breastfeeding, or plan to conceive within 3 monthsPatients with concurrent serious diseases, such as cancer, serious cardiovascular, respiratory, hepatic, renal, or neurological diseasePatients who are participating or who have participated in another clinical trial within the previous 3 monthsPatients who, in the opinion of the researcher, are unsuitable for the trial

### Randomization

A block randomization sequence will be created by an independent statistician, using SAS 9.2 software (SAS Institute Inc., Cary, USA). The randomization will be stratified by site with eligible participants randomly assigned to either the TCKM granule group or the placebo group at a ratio of 1:1. Researchers will access the treatment allocation for each eligible participant through a remote and web-based randomization system, which has been developed by the Key Unit of Methodology in Clinical Research, GPHCM. A label with a serial number based on the randomization schedule will be attached to all drugs. Treatment allocations will be kept in password-protected files and saved by an independent staff member.

### Blinding

Treatment allocations will be blinded to the participants, clinicians, research assistants, drug managers, statisticians, and other staff members, and will not be revealed until the study is completed. After a run-in period, the clinicians will assess whether the patients are still eligible. For each eligible patient, the clinician will apply for a randomized assignment by logging into the web-based randomization system, and write a prescription for “TCKM granules, three bags, twice a day.” Then, accompanied with a research assistant, the patients will be taken to the appointed drug managers at the GPHCM pharmacy. The drug managers are responsible for dispensing medication according to the prescriptions and assignments. During the trial periods, clinicians, research assistants, and drug managers are forbidden from discussing the assignment possibilities with the participants. The placebo granules have an appearance, smell and taste similar to the TCKM granules. All drugs are packaged in an identical manner. The blinding codes will be kept strictly confidential, and will not be broken during the trial unless serious adverse events occur. The date and reason for breaking the blinding code will be recorded in the case report forms (CRFs).

### Intervention

Health education. The participants in both groups will receive a health education course. Health education handbooks will be provided by research assistants, and will include a series of IBS-related information, such as pathophysiological mechanisms, causative factors, and prognosis. After reading their handbooks, the participants can discuss the material with the clinicians. Diet- and stress-related issues among IBS patients will be discussed in detailsExperimental drugs and placebo. Participants will receive three bags of either the TCKM granules or the matched placebo granules twice a day for 4 weeks. The placebo consists primarily of lactose, maltodextrin, natural food coloring and sucrose octaacetate. The experimental granules and the placebo granules are identical in appearance, taste, smell, weight, and packaging. Both of them will be provided by the Tianjiang Pharmaceutical Co., Ltd. (Jiangyin, Jiangsu Province, China) which meets the requirements of the Good Manufacturing Practice (GMP). All herbs will be obtained from qualified suppliers in ChinaRescue medication. If patents’ diarrhea and abdominal pain are exacerbated beyond a tolerable level, rescue medication will be allowed for relieving abdominal symptoms in both groups. Montmorillonite powder, berberine hydrochloride, and levofloxacin will be allowed for uncontrollable diarrhea; and pinaverium bromide will be allowed for uncontrollable abdominal pain. Concomitant use of two or more rescue medications will also be allowed, and their dosages will depend on the symptoms severity. However, the administration of the rescue medication must be limited within 3 days, or the patients will be considered as withdrawn. In such cases, the name, dosage, and duration of the rescue medication are to be documented in the symptom diaries and CRFs

#### Secondary outcomes

##### Relief and relapse incidents

The definition of relapse is the recurrence of abdominal pain/discomfort or diarrhea in IBS patients who have achieved treatment success. Achieving treatment success means that IBS symptoms have been relieved, and the relief has lasted at least 1 week after treatment. Relief and relapse incident outcomes include time until relief, time until first relapse, and total relapse times. Time until relief is defined as the time from patients receiving treatment to achieving treatment success. Time until first relapse is defined as the time from patients achieving treatment success to the recurrence of abdominal pain/discomfort or diarrhea. Total relapse times refer to the sum of relapse times during both the treatment period and the follow-up period.

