### Sample size calculation

The sample size for this trial was calculated based on the primary outcome—the proportion of responders of AR, using PASS 11.0 software (NCSS, LLC, Kaysville, UT, USA). Combining our previous observational study with similar studies [28, 29], we assume that the proportion of responders of AR in TCKM granule group will be 60%, and in the placebo group 30%. Fifty-seven patients in each group can achieve 90% power and rule out type I error of 5% by using a two-sided test. We expect that 20% of the participants may be lost to follow-up. Therefore, the sample size in each group should be adjusted to 72. In total, 144 participants will be enrolled in this trial.

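### Relapse can occur only after treatment success, so total relapse times and time until first relapse do not give a fair randomised comparison of relapse

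*Protocol article*

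**What the plan says.** All three relief and relapse outcomes are defined under Relief and relapse incidents in the protocol article. Relapse is conditional on success: "The definition of relapse is the recurrence of abdominal pain/discomfort or diarrhea in IBS patients who have achieved treatment success". Success is defined as follows: "Achieving treatment success means that IBS symptoms have been relieved, and the relief has lasted at least 1 week after treatment". The count is a plain sum: "Total relapse times refer to the sum of relapse times during both the treatment period and the follow-up period". The time outcome starts its clock at success: "Time until first relapse is defined as the time from patients achieving treatment success to the recurrence of abdominal pain/discomfort or diarrhea".

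The section does not say how a patient who never reaches success enters the count, and it does not mention time at risk. Statistical analysis names the intention-to-treat and per-protocol populations, neither of which is restricted to successes. For continuous variables at each time point it offers a *t* test or a Wilcoxon-Mann-Whitney test. No test is named specifically for a cumulative relapse count.

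Relapse matters to the stated aims. The first objective under Trial purpose is efficacy and safety, "especially in reducing IBS symptom" relapse. The Discussion presents these definitions as possibly better suited to assessing relapse than repeated visit measures.

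**The concern.** A patient with symptoms for all 16 weeks cannot relapse under this definition. In an intention-to-treat comparison that patient contributes 0, the same as a patient who was relieved early and stayed well. A treatment that relieves more patients puts more of them at risk of relapse, and one that relieves them sooner gives them longer at risk. Both push the raw count up in the better arm.

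Leaving the never-relieved patients out creates a different problem. The comparison is then between patients selected by their response after randomisation, and a larger share of one arm is selected than of the other. Time until first relapse is always of this kind, because a patient without success has no starting point.

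At stake is whether the trial can support a statement about relapse reduction, which its first objective singles out.

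**Working it through.** **Inputs from the protocol article.**
- Adequate-relief response of 60% on TCKM and 30% on placebo; 57 per group before and 72 per group after allowance for 20% loss (Sample size calculation).
- 4 weeks of treatment and 12 weeks of follow-up (Design).

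**Inputs assumed.**
- Success rates equal to the adequate-relief rates, then varied. Success and adequate-relief response are different definitions.
- *m*, the mean number of relapses per successful placebo patient: 1.2 (0.10 per week over 12 weeks), then 0.3. The article gives no figure.
- RR, the ratio of relapses per successful patient, TCKM to placebo.
- Poisson counts in successes, 0 in all others, and a two-sided Mann-Whitney test at 5%.

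**Step 1: the plan's own figure.** The article states: "Fifty-seven patients in each group can achieve 90% power and rule out type I error of 5% by using a two-sided test". With the pooled normal approximation,

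n = [1.96 × √(2 × 0.45 × 0.55) + 1.2816 × √(0.6 × 0.4 + 0.3 × 0.7)]² / 0.30² = 55.7, so 56 per group.

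Power at 57 per group is 90.7%. Then 57/0.8 = 71.25, so 72 per group and 144 in total. The sample size reproduces to within one patient per group and is not in question.

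**Step 2: mean count per randomised patient.**
- TCKM: 0.60 × *m* × RR. Placebo: 0.30 × *m*.
- With RR = 1 and *m* = 1.2: 0.60 × 1.2 = 0.72 on TCKM and 0.30 × 1.2 = 0.36 on placebo.
- At these rates 40% of TCKM and 70% of placebo patients are fixed at 0.

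**Step 3: break-even.** The means are equal when RR = P(success, placebo) / P(success, TCKM), whatever *m* is.

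| Success, TCKM v placebo | Break-even RR | TCKM mean is higher unless it cuts relapses per success by more than |
|---|---|---|
| 60% v 30% | 0.50 | 50% |
| 60% v 40% | 0.67 | 33% |
| 80% v 60% | 0.75 | 25% |
| 50% v 40% | 0.80 | 20% |

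**Step 4: test results with no true effect on relapse (RR = 1).**

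| Success | *m* | Per arm | Significant against TCKM |
|---|---|---|---|
| 60% v 30% | 1.2 | 72 | about 76% |
| 60% v 30% | 1.2 | 57 | about 66% |
| 60% v 30% | 0.3 | 72 | about 30% |
| 80% v 60% | 1.2 | 72 | about 35% |
| 50% v 40% | 1.2 | 72 | about 13% |

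**Step 5: test results with a true benefit on relapse (60% v 30%, *m* = 1.2, 72 per arm).**
- True cut of 30%: about 36% of trials significant against TCKM, essentially none in favour.
- True cut of 50%: about 10% against, under 1% in favour.
- True cut of 70%: under 1% against, but only about 8% in favour.

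**Step 6: successes only.** With 57 randomised per arm, *m* = 2 and RR = 1, a comparison restricted to successes is significant against TCKM in 2.4% of trials and in favour in 2.8%. The artefact disappears, but only because the simulation gives successes in both arms the same underlying tendency to relapse. Randomisation does not guarantee that once selection is on response.

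**The case against.** **The zero score is not stated.** The definition can be read as an outcome among successes only, and the statistical analysis plan, which is not shown, could fix the analysis set. This stands as a limit on the simulated figures. It does not remove the problem, because exclusion replaces a perverse score with a comparison of non-randomised subsets. The size of that second bias cannot be derived from the document.

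**The figures depend on inputs.** This also stands. Adequate-relief response needs two positive answers in 4 weeks. Success needs relief lasting 1 week, with no stated 4-week limit, so more patients in both arms may reach it and the gap may narrow. At 80% v 60% success and a true halving of relapse, a separate run gave 18% of trials in favour of TCKM and none against. The relapse rate and the choice of test are assumptions too.

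**Durability is already covered.** Long-term effectiveness (adequate relief in at least six of 12 follow-up weeks) can be determined in all patients, and a never-relieved patient fails it. That is a real mitigation, although it measures weeks of relief in follow-up and not relapse.

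**The wording on timing.** A reader might infer from "the relief has lasted at least 1 week after treatment" that success can be reached only after the 4-week course, so that no relapse could ever be counted in the treatment period. The rest of the section does not support this: time until relief runs from receiving treatment, and relapses in the treatment period are expressly included. The consistent reading is after treatment starts, so this calls only for clarification.

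**Conclusion.** The concern holds with limits. As defined, neither total relapse times nor time until first relapse gives a fair randomised comparison of relapse, whichever way never-relieved patients are handled. If they score 0, the raw count is tilted against the arm with more successes. The direction needs only a higher success rate on TCKM. The size depends on the success gap and the relapse rate: with no true effect on relapse, the chance of a significant result against TCKM ranged from about 13% to about 76% over the inputs tried with 72 per arm.

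A reader might infer that an effective drug must look worse. The document does not support that. At 60% v 30% the means reverse only if the true cut in relapses per success is less than half; with a 70% cut there is no reversal, but the test rarely detects the benefit.

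A reader might also infer that the trial's main conclusion is compromised. It is not: these are secondary outcomes, adequate relief is primary and drives the sample size, and long-term effectiveness covers all patients. The change should be made, but the trial does not stand or fall on it.

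**What to change.** 1. Make the main relapse-related secondary outcome one that is defined in every randomised patient, from the daily diaries and adequate-relief answers. Either relieved and not relapsed by week 16 (yes/no, never-relieved patients counted as failures) or weeks in relief from randomisation to week 16 (never-relieved patients counted as 0) would do.
2. Report total relapses as a rate per week in remission, for example from a negative binomial model with log time at risk as offset. Label this rate and time until first relapse as descriptive in the relieved subset, and give the number of patients in that subset by arm.
3. State that the success clock runs from the start of treatment, so that the definition agrees with counting relapses in the treatment period.

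The cost is some wording and one derived variable. Diaries are kept throughout the study, and Trial status says that recruitment is still in preparation. The downside is that the outcomes in item 1 blend achieving relief with keeping it, so they cannot isolate an effect on relapse alone. The descriptive results in item 2 help the reader to judge that part.
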